## Supplement 1. Trial protocol

### Effects of a Mobile Instant Messaging – Delivered Psychoeducational Intervention for Cancer Caregivers

#### Background

Adolescent and young adult (AYA) cancer patients are a segment of the cancer population that warrants additional attention. Various age ranges have been used to define AYA cancer patients, but they are commonly defined as those diagnosed with cancer from 15 to 39 years of age. This definition will be adopted in this study to facilitate comparisons with other studies of AYA cancer patients. In 2020, there were almost 1.2 million AYA cancer cases worldwide, accounting for 6.5% of the total cancer patient population. Of these cases, one fifth (255,316 cases) were reported in China. Although AYA cancer patients constitute a relatively small proportion of the entire cancer population, an increasing trend in AYA cancer incidence rates has been observed in recent decades. In addition, with more than 1 million new cancer diagnoses annually in the AYA population worldwide, the cancer incidence is increasing at a higher rate in this population than in other age groups. These features suggest that AYA cancer patients will constitute an increasing proportion of the total cancer population in the future. Furthermore, the overall 5-year survival rate ranges from 83% to 86% across AYA age groups, which is similar to the survival rate in children (84%), but higher than that in adults over 40 years old (66%). However, the 5-year survival rate varies considerably among cancer types in the AYA population. For example, Hodgkin's lymphoma has a 5-year survival rate of 94%, but acute lymphocytic leukemia has a 5-year survival rate of 60%. Overall, most AYA cancer patients require long-term caregiver support.

Caregivers are the primary source of help and support for patients and are typically family members, partners, or close friends. They also require attention from healthcare providers, as a cancer diagnosis affects both the patients and their caregivers, who can be considered as secondary patients. For caregivers of AYA cancer patients, a cancer diagnosis is a significant source of stress and requires a demanding long-term role. Throughout the post-diagnosis course of cancer, the caregivers of AYA cancer patients continue to play crucial roles by offering assistance in daily life activities; communicating with healthcare providers; dealing with medical needs; and providing financial, emotional, and spiritual support to the patients. However, the stress they encounter varies during the different phases of the cancer trajectory, which includes pre-diagnosis, diagnosis, treatment, survivorship, recurrence, and advanced/end-of-life phases. For example, the treatment phase starts from the time of diagnosis and during the initial visit to the outpatient clinic until the last cycle of therapy. The duration of the treatment phase varies based on factors such as the type of cancer, cancer stage, drugs administered, and treatment side effects. Typically, this phase lasts a few months. During this phase, the caregivers confront the unfamiliar scenario of the treatment of the AYA cancer patient. They have to worry about the patients' treatment tolerance and the effectiveness of the treatment. The caregivers also provide physical care to the patients and manage their symptoms, while attempting to strike a balance between their caregiver roles and their other family and social roles. Additionally, the caregivers need to address the AYA patients' unique psychosocial needs, such as fertility preservation, parenting, and education. Therefore, the treatment phase is one of the most stressful phases for caregivers.

As they are often under tremendous stress during the treatment of AYA cancer patients, caregivers have many unmet needs. Unmet needs refer to the caregivers' requirements or needs related to problems or issues for which they are unable to obtain assistance. Few caregivers receive training related to their caregiver role, and caregivers consistently report an insufficient level of support available for them, as most resources are directed toward the patients. Consequently, the caregivers of AYA cancer patients often have many unmet needs, mainly psychosocial needs, informational needs, and needs related to practical support and their relationship with the AYA cancer patient. Of the aforementioned needs, these caregivers report the highest demand for informational and emotional support. However, evidence is scarce regarding the unmet needs of caregivers of AYA cancer patients in China, where routine support for caregivers is not widely available in most hospitals. It has been reported that only 5.6% of the caregivers of adult cancer patients have no needs or have all their needs met. As cultural differences may effect caregivers' experience in terms of their appraisal of stressful events, perceptions of roles and caregiving responsibilities, perception and use of family support, and coping behaviours, it is crucial to explore the unmet needs of caregivers of AYA cancer patients in different cultural contexts.

When caregivers face unmet needs during the caregiving process, they adopt coping strategies to deal with their situation. The specific coping strategies used can vary depending on the context. One study found that the caregivers of AYA cancer patients were more likely to adopt coping strategies,

such as problem solving, cognitive restructuring, expressing emotions, and social contract, than other strategies, including problem avoidance, wishful thinking, self-criticism, and social withdrawal. Nevertheless, most caregivers demonstrate inadequate coping strategies.

According to stress and coping theory, an individual's health is affected by their appraisal, coping, and interactive processes during stressful events. Of the various factors that affect caregivers' appraisal of stress, unmet needs are particularly important. Consequently, caregivers' unmet needs and inadequate coping negatively influence their health. Previous studies have found that approximately one in three caregivers of AYA cancer patients have moderately to severely elevated anxiety and depressive symptoms. Caregivers have also reported reduced quality of life after taking care of patients.

Given the needs of caregivers of AYA cancer patients and the negative effects that they experience, support for these caregivers is essential. The National Cancer Institute recently emphasized the importance of developing interventions tailored to the caregivers of AYA patients, given their unique life course and social needs. However, the majority of currently available interventions focus on the caregivers of older adult cancer patients, because the prevalence of cancer is higher in the population aged above 40 years. Few interventions are specifically designed for the caregivers of AYA cancer patients. Therefore, additional research on interventions for caregivers of AYA cancer patients is warranted to address their unmet needs and improve their health.

Psychoeducational interventions (PEIs) are commonly used interventions to address the needs of and challenges faced by caregivers of cancer patients. Given the various unmet needs reported by caregivers of AYA cancer patients, particularly their informational and emotional needs, a PEI may be a suitable type of intervention, as it provides information and deals with the emotional and psychosocial needs of caregivers. Previous studies have shown that a PEI is a cost-effective strategy to improve the outcomes of caregivers of cancer patients, such as meeting their needs, relieving their psychological stress, and enhancing their quality of life. However, to the best of our knowledge, there has been no research on PEIs for AYA cancer patients. The content of PEIs for caregivers of cancer patients in other age groups may not be directly applicable to caregivers of AYA cancer patients. In addition, caregivers' suboptimal health needs to be addressed. Therefore, in this study, we will develop a mobile instant messaging-delivered PEI for caregivers of AYA cancer patients and examine its effectiveness.

## **Methods**

### **Design**

A two-arm (parallel-group) randomized controlled trial with repeated measurements will be conducted. Eligible caregivers of AYA cancer patients will be invited to participate. After their written informed consent is obtained and baseline data collection is completed, the participants will be randomly allocated to the intervention or control group at a 1:1 ratio using a randomized block design, with block sizes of four or six. Sequentially numbered, opaque, sealed envelopes will be used to guarantee allocation concealment. The participants in the intervention group will receive the mobile instant messaging-delivered PEI and usual care, while those in the control group will receive usual care. The outcomes (anxiety, depression, quality of life and coping) will be reassessed 5 weeks (immediately after the intervention) and 12 weeks after baseline. Unmet needs will be reassessed 5 weeks after baseline. A repeated measurement design of three time points with 12 weeks of follow-up will be used, because a 12-week follow-up period has been shown to be sufficient to observe changes in the outcomes of interest in this study. The outcomes will be remeasured 5 weeks after baseline (immediately after the intervention) to evaluate whether the intervention had any immediate effects.

### **Setting and Participants**

#### **Setting**

The study participants will be recruited from the inpatient wards of a tertiary cancer hospital in Changsha, Hunan Province, China.

#### **Sampling Method**

Potential participants will be the caregivers of AYA cancer patients in the treatment phase. They will be recruited using convenience sampling and included if they: 1) caregivers caring for AYA cancer patients during the treatment phase; 2) are still caring for the patients after discharge; 3) aged at least 18

years; 4) caregivers who have at least one item with a high level of unmet need in the needs assessment; 5) can understand the research project and can read and communicate in Chinese; 6) are reachable via the mobile instant messaging application (WeChat); and 7) provide informed consent to participate in this study. If two or more caregivers are available for a given patient, the one undertaking the primary caregiving responsibility will be included. The principal investigator (PI) or the research assistants, who are responsible for recruiting, will ask the doctors about the expected duration of treatment for the AYA cancer patients, to ensure that they will be undergoing treatment throughout the study period. Caregivers excluded if: 1) they are being paid; 2) the AYA cancer patient under their care is receiving hospice care; 3) they are mentally unstable or have cognitive impairments that result in an inability to participate in the intervention; or 4) they are participating in another research interventional program.

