Caregivers' informational needs are mainly related to the patient's disease, common treatments, treatment side effects, managing the illness at home, communicating with healthcare professionals, and talking about the illness with the patient. The financial needs mainly involve their need to pay non-medical costs and to receive financial assistance. As we cannot provide direct financial assistance to the caregivers, information about medical insurance and relevant financial assistance programs will be provided. These need-oriented contents will be delivered over five weekly sessions, based on what the caregivers may need each week. For example, in the first week, when the caregivers may need to care for the patients in the hospital, the intervention contents will mainly aim to help the caregivers deal with the medical needs of the patient during their stay in the hospital. Information about the patient's disease, treatments, and treatment side effects; medical insurance and financial assistance programs; how to obtain medical services; and how to communicate with healthcare professionals effectively will be provided in the first week. The contents of each session of the PEI with respect to unmet needs are presented in Table 1.

The whole intervention will be delivered by the PI to ensure intervention consistency. The five sessions of the intervention will be conducted via a mobile instant messaging application, the most popular social media platform in China. This platform allows free instant messages to be sent to individuals or groups through articles and video calls. The first session will be initiated within 1 week

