### **Data Collection Procedures**

Before baseline data collection, the PI and the research assistants responsible for participant recruitment will assess the unmet needs of the potential participants to determine their eligibility. The eligible participants who consent to participate in the study will be invited to complete questionnaires to perform the baseline assessment. The participants will complete their baseline assessment by filling out paper questionnaires on-site. Follow-up assessments will then be conducted 5 weeks (T1) and 12 weeks (T2) after the baseline assessment. e-Questionnaires will be used for follow-up data collection. The contents of the corresponding questionnaires at each follow-up time point will be input into an e-questionnaire platform (<https://www.wjx.cn/>). The link containing these questionnaires will then be sent to each participant individually through the mobile instant messaging application. The participants will complete the questionnaires independently, given that all questionnaires used in this study are self-reported. To facilitate the participants returning the e-questionnaires on time, the PI will send reminder messages if the questionnaire is not completed on that day. In addition, they will be asked to enter the study ID assigned to them, instead of their names, to protect their privacy. The PI will determine who has completed the questionnaire by identifying their unique study ID. After the participants complete the questionnaires, the PI will thoroughly review the responses for any instances of duplicate records or consecutively consistent answers. If the participants provide consistent answers for ten or more consecutive questions, it will be deemed as straightlining. To ensure the accuracy of the responses in such cases, a research assistant, who is unaware of the intervention allocation, will contact the participants and confirm their responses to these questions.

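### The PI may recruit and judge eligibility while also delivering every intervention session, so allocation in blocks of four or six is partly predictable to one recruiter

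*Protocol*

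**What the plan says.** Four parts of the protocol bear on this.

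- **Recruitment (Sampling Method).** The recruiters are "The principal investigator (PI) or the research assistants, who are responsible for recruiting". Sampling is by convenience. Some criteria need judgement, such as mental instability, the ability to understand the project, and which of several caregivers carries the main responsibility.
- **Eligibility (Data Collection Procedures).** Before baseline, "the PI and the research assistants responsible for participant recruitment will assess the unmet needs of the potential participants to determine their eligibility".
- **Delivery (Intervention Group).** "The whole intervention will be delivered by the PI to ensure intervention consistency". The first session begins within a week of recruitment. The PI also tracks questionnaire completion by study ID (Data Collection Procedures).
- **Allocation (Design).** Participants are "randomly allocated to the intervention or control group at a 1:1 ratio" "using a randomized block design, with block sizes of four or six". The safeguard is stated as "Sequentially numbered, opaque, sealed envelopes will be used to guarantee allocation concealment". The order is also given: "After their written informed consent is obtained and baseline data collection is completed, the participants will be randomly allocated".

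The trial has one hospital (Setting), and no stratification is stated. The protocol does not say who prepares, holds or opens the envelopes, what share of participants the PI recruits, or how fast accrual is expected to be. It does not bar the PI from recruiting once allocations are known.

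**The concern.** Concealment has two parts: the next assignment must be hidden, and it must not be predictable from those already made. Numbered, opaque, sealed envelopes deal with the first part only. The PI treats every intervention participant, so knows who is in that arm. Because the PI also follows all participants by study ID, the PI can work out by exclusion who is in the control arm. One hospital and no stated stratification mean that there is a single sequence to follow.

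With short balanced blocks the running difference between the arms returns to zero at each block end, so the arm that is behind is the better guess. A recruiter with that knowledge could, without intending to, approach a caregiver sooner, later or not at all, or lean one way on a criterion that needs judgement. Randomizing after consent and baseline protects the baseline answers, but not the earlier choice of whom to approach or judge eligible.

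The primary outcomes, GAD-7 and PHQ-9, are self-reported by caregivers who know whether they are receiving the sessions. Selection on unmeasured traits such as motivation could not be fully repaired in the analysis.

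**Working it through.** **Inputs from the protocol.** Ratio 1:1, block sizes 4 or 6, sequence length 160 (80 per group), one hospital, no stratification stated. The protocol gives no guess probability, so there is no stated figure to reproduce.

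**Assumptions.** (a) Each new block is of 4 or 6 with equal chance; the protocol does not give the mix, so both pure cases are shown as well. (b) The recruiter guesses the arm with fewer allocations so far and tosses a coin when the arms are level. (c) At first, every earlier allocation is known, in order. This is relaxed below.

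**Formula.** For a block of size 2m, the expected number of correct guesses is m + (4^m / C(2m, m) − 1)/2.

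- Blocks of 4 (m = 2): 2 + (16/6 − 1)/2 = 2.833, and 2.833/4 = **70.8%**.
- Blocks of 6 (m = 3): 3 + (64/20 − 1)/2 = 4.10, and 4.10/6 = **68.3%**.
- One block of each: (2.833 + 4.10)/10 = 6.933/10 = **69.3%**.

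**Check by enumeration.** The chance of a right guess at each position is 1/2, 2/3, 2/3, 1 in a block of 4 (sum 2.833) and 0.5, 0.6, 0.6, 0.7, 0.7, 1 in a block of 6 (sum 4.10). Both sums agree with the formula.

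**Mixed blocks with boundaries unknown.** Simulating 4,000 sequences of 160 gives 69.2% (Monte Carlo standard error 0.02 percentage points). This holds both for an optimal Bayesian guess and for the simple rule of guessing the arm that is behind. Not knowing the block boundaries therefore hardly changes the average. What it does reduce is the share of allocations known with certainty:

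| Sequence | Average correct | Known with certainty |
|---|---|---|
| All blocks of 4 | 70.8% | 33% |
| All blocks of 6 | 68.3% | 25% |
| Equal mix, boundaries known | 69.3% | 28% |
| Equal mix, boundaries unknown | 69.2% | about 5.5% |

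**Delayed knowledge.** The first session may start up to a week after recruitment, so the most recent allocations may not yet be known to the PI. Simulating the same rule for the equal mix, with the latest allocations hidden from the guesser:

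| Latest allocations not yet known | Correct guesses |
|---|---|
| 0 | about 69% |
| 1 | about 59% |
| 2 | about 56% |
| 3 | about 52% |
| 4 | about 51% |
| 5 | about 50% |

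The number of allocations hidden at any time depends on the accrual rate and on who opens the envelopes. The protocol gives neither, so for the mix the supported range is about 50% to 69%. A PI who opened the envelopes would be at the top of it.

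**The case against.** A reader might infer that the PI will guess the next arm about 70% of the time, or that concealment has failed. The documents support neither.

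- **The 70% is a ceiling.** It needs one recruiter who knows every earlier allocation, in order, before each approach. No sentence says that this is so. It is inferred by reading the recruitment, delivery and follow-up sections together, and the recruitment sentence alone does not show it. One unknown recent allocation already takes the figure for the mix to about 59%. This objection stands.
- **Only part of recruitment is affected.** The protocol says the PI or the research assistants, and the assistants do not deliver the intervention. The effect on the whole trial is diluted by an unknown amount. This also stands.
- **The planned safeguards are real.** Sealed envelopes hide the next assignment, randomization follows consent and baseline, and two block sizes leave few allocations certain when boundaries are unknown. To say that concealment is undermined would be too strong. Partly predictable to the PI is accurate.
- **No bias in the outcomes is shown.** A guessing rate is not a shift in GAD-7 or PHQ-9. Several criteria leave little discretion (age, unpaid status, use of the messaging application, a need item scored 3 or more). The GEE model in Data Analysis includes baseline, so selection on baseline severity would be partly absorbed. This stands as a limit on size, but it does not cover unmeasured traits, the choice of whom to approach, or the criteria that need judgement.

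What remains is that the protocol permits one person to hold both roles and requires no delay in that person's knowledge. Envelopes do not address that.

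**Conclusion.** The point holds as a weakness in how duties are assigned. The protocol allows the PI to recruit and judge eligibility while treating every intervention participant, in one unstratified sequence of short blocks. Allocation is then partly predictable to the PI: at most about 69% for a mix of the block sizes (70.8% if all are of four, 68.3% if all are of six), declining to 50% once the five latest allocations are unknown.

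The size rests on an equal mix of block sizes, on the PI knowing the control allocations by exclusion, and on an accrual rate and envelope procedure that the protocol does not give. It applies only to participants whom the PI recruits. It shows an opportunity for selection bias, not that bias will occur, and it does not affect the sample size. It should be changed because the remedy costs little and the bias, if it arose, could not be fully corrected afterwards.

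**What to change.** In Sampling Method and Data Collection Procedures, assign screening, eligibility judgement, invitation and consent to the research assistants, who already share this work, and state that they are kept unaware of earlier allocations. In Design, state that someone other than the PI opens and logs each envelope, and that the PI learns an allocation only after that participant's baseline is complete and the envelope has been logged. The protocol already uses an assistant unaware of allocation to confirm suspect questionnaire answers, so the arrangement is not new to the trial.

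The cost is a change of duties among existing staff, with no added participants and no change to outcomes or analysis. The downside is less flexible recruitment when the assistants are absent.

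Withholding block sizes from recruiters is at most a minor addition. Guessing the arm that is behind needs no knowledge of block boundaries, and the average rate is 69.2% without that knowledge against 69.3% with it.

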### **Sample Size Planning**

The sample size was calculated based on the primary outcomes (anxiety and depression) using G-power (version 3.1.9.7; Heinrich-Heine-Universität Düsseldorf, Düsseldorf, Germany). Considering that no similar study has been conducted for caregivers of AYA cancer patients, the effect sizes of the primary outcomes in previous studies of PEIs for caregivers of adult cancer patients were used to calculate the sample size. The combined effect size for anxiety in previous studies was  $-0.50$ . For a two-tailed  $\alpha$  error of 5%, 80% power, and a test of two independent groups, the required sample size for each group was calculated as 64. An acceptable attrition rate has been shown to be less than 20%. Thus, we assumed an attrition rate of 20% for this study. As a result, the final sample size was calculated as 160 for the two arms. The effect size for depression in previous studies was  $-0.54$ . Based on this effect size, the final sample size was calculated as 138, when using the same parameters as those used for the anxiety outcome. We adopted a larger sample size to guarantee sufficient statistical power. Therefore, the required sample size in this study is 160, with 80 in each group.

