### **Data Analysis**

All data will be analyzed using SPSS 26.0 (IBM Corp., Armonk, NY, USA). Continuous data will be tested for normality by assessing skewness and kurtosis and by a visual inspection of Q-Q plots. The sociodemographic data and the caregivers' outcomes will be presented using descriptive statistics, as appropriate. The data will be described as means and standard deviations if normally distributed or medians and interquartile ranges if non-normally distributed. Categorical variables will be expressed as numbers (n) and percentages (%). The skewed variables will be appropriately transformed as necessary before testing the intervention effects. A generalized estimating equations (GEE) model will be used to explore the effects of the mobile instant messaging-delivered PEI on the outcomes of interest in this study. The effects of the intervention on the outcome variables will be compared across three time points, namely, T0 (baseline), T1 (5 weeks after baseline), and T2 (12 weeks after baseline) or two-time points (T0 and T1), as appropriate. The control group (assigned as 0) and the baseline (assigned as 0) will be set as the references in the GEE model. The intention-to-treat principle will be followed. The homogeneity between the participants who complete the study and those who drop out will be compared using an independent Student's t-test, Mann-Whitney U test, chi-square test, or Fisher's exact test, as appropriate. If the missing data are deemed to be missing at random, they will be left unaddressed, because GEE models allow data to be missing at random and yield valid results by analyzing the observed data. Otherwise, multiple imputation will be used to impute the missing data.

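### Two primary outcomes are each sized at the full two-sided 5% and measured at two follow-ups, with no primary time point, order or alpha split, so the 5% and 80% apply only to one outcome at one time

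*Protocol*

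**What the plan says.** - **Primary outcomes.** Sample Size Planning: "The sample size was calculated based on the primary outcomes (anxiety and depression"). The Primary Outcomes section lists the same two, measured by GAD-7 and PHQ-9.
- **Sizing.** Anxiety is sized for an effect of −0.50 with a two-sided "error of 5%, 80% power, and a test of two independent groups", giving 64 per group and 160 in total after 20% attrition. Depression is sized for −0.54 with identical settings, giving 138. The section then states: "We adopted a larger sample size to guarantee sufficient statistical power". It does not say which follow-up time the calculation refers to.
- **Timing.** Design: "The outcomes (anxiety, depression, quality of life and coping) will be reassessed 5 weeks (immediately after the intervention) and 12 weeks after baseline". The section gives a reason for the 12-week follow-up length and says the week-5 measurement is for immediate effects. It calls neither time primary.
- **Analysis.** Data Analysis plans a GEE model in which effects "will be compared across three time points", with the control group and baseline as reference levels. It gives no significance level, no order of testing, and no rule on whether one outcome or both must be positive.

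**The concern.** A sample size is computed for a particular comparison. Here it is computed twice, each time spending the whole 5%, and the comparison is tied to neither follow-up. The analysis can then produce a group effect for two primary outcomes at two times, and nothing says which of these decides the trial.

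If any one positive result were enough, the chance of a false claim would exceed 5%. If both outcomes had to be positive, the chance of success would be below 80%. Leaving the rule open until results are available would also allow the more favourable outcome or time point to be put forward as the primary finding.

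**Working it through.** **Inputs from Sample Size Planning:** d = 0.50 (anxiety) and 0.54 (depression) in absolute value; two-sided alpha 0.05; power 0.80; two independent groups; attrition 20%. Allocation is 1:1 (Design). Correlations between outcomes and between times are not given, so those below are assumptions.

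**1. The protocol's own figures.** Two-sample t test, non-centrality d·√(n/2), 2n − 2 degrees of freedom.
- Anxiety: power is 79.5% at n = 63 and 80.1% at n = 64 (0.50·√32 = 2.83). 64/0.8 = 80 per arm, 160 in total.
- Depression: power is 79.4% at n = 54 and 80.1% at n = 55. 110/0.8 = 137.5, rounded up to 138.
- Depression at 64 per arm: 0.54·√32 = 3.05, power 85.8%.

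Both stated totals reproduce exactly.

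**2. Family-wise error if any win counts, each test at 5%.** With k independent tests it is 1 − 0.95^k: 9.75% for k = 2 and 18.5% for k = 4. With correlated test statistics it is 1 − P(all |Z| ≤ 1.96), simulated from a multivariate normal distribution:

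| Assumed correlation | Two tests (one per outcome) | Four tests (two outcomes × two times) |
|---|---|---|
| 0 | 9.7% | 18.5% |
| 0.5 | 9.1% | 15.6–16.1% |
| 0.7 | 8.3% | 13.0–13.7% |
| 0.9 | 7.0% | 9.4–9.8% |

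In the last column, the lower value takes all four statistics as equally correlated. The higher takes the cross-outcome, cross-time correlation as the product of the other two.

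**3. Joint power if both outcomes were required at one time.** 64 per arm, each at 5%, t test on follow-up values only. Independent: 0.801 × 0.858 = 0.69. Simulated: 73% at correlation 0.5, 75% at 0.7, 78% at 0.9.

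**4. Cost of dividing alpha later at the committed size.**
- 2.5% per outcome: power at 64 per arm is 71.2% (anxiety) and 78.3% (depression). Restoring 80% for anxiety needs 78 per arm; 78/0.8 = 97.5, rounded up to 98, or 196 in total.
- 1.25% for each of four tests: anxiety power is 61.6%. Restoring 80% needs 91 per arm; 91/0.8 = 113.75, rounded up to 114, or 228 in total.

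**5. Fixed sequence, anxiety then depression, each at 5%, one time point.** Family-wise error is 5%. Anxiety power stays at 80.1%. Depression can be claimed only when both tests are significant, so its power is the joint power of step 3: 69–78%, against 85.8% when tested alone.

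**The case against.** The strongest reply is that testing order and multiplicity rules are usually left to a statistical analysis plan, which is not at hand, and that no sentence in the protocol is shown to be false. This stands in part: the absence of a multiplicity rule would not by itself be a finding. But the protocol fixes the sample size by using the full 5% twice. If an unseen plan divided alpha equally between the outcomes, anxiety power would fall to 71% at that size.

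Several stronger readings are tempting and go further than the document:
- **Four primary tests, each at 5%, any of which can be claimed.** Data Analysis states no alpha; the 5% appears only as a sample-size input. Four tests are inferred from the reference coding of the GEE. One joint group-by-time test per outcome would leave two. No success rule is written down.
- **The stated 5% and 80% cannot both hold.** They hold exactly per outcome. At trial level, 160 participants satisfy both for anxiety under a fixed sequence. They also suffice for a win on at least one outcome at 2.5% each: 1 − (1 − 0.712)(1 − 0.783) = 94% if independent, 81% at correlation 0.9.
- **The promise of sufficient power is broken because both outcomes must succeed.** No both-must-win rule is stated, and the sentence in question only explains choosing 160 over 138.

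The joint-power figures also rest on a follow-up-only t test. If the baseline-referenced GEE contrast behaves like a change score, d becomes d/√(2(1 − ρ)), where ρ is the baseline-to-follow-up correlation. For independent outcomes, joint power is then 57%, 69% or 81% at ρ = 0.4, 0.5 or 0.6. Since ρ is not given, a shortfall below 80% is conditional on the method assumed.

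**Conclusion.** The point holds as a trial-level gap and is a should-fix. The sample size is not miscalculated. The protocol gives each of two primary outcomes the full 5%, follows both at two times, and never selects the comparison to which its error rate and power belong.

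If a win on either outcome counts and each test is at 5%, family-wise error is about 7–10% with one test per outcome, or about 9–19% if both follow-up contrasts are tested. The range reflects assumed correlations from 0.9 down to 0, and the higher range also depends on the four-test reading. If both outcomes were required, joint power would be about 69–78% under the t test used for sizing. A reader might infer that the planned size is unworkable; it is not, because a short statement of the primary comparison makes 160 consistent with 5% and 80% for anxiety.

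**What to change.** Before outcome data are seen:
1. Name one primary time point. Week 12 is reasonable given the follow-up rationale in Design, but that section does not itself rank week 12 above week 5, so the sponsor must make the choice explicitly.
2. In Data Analysis, state that anxiety is tested first at that time point at a two-sided 5%, and depression at a two-sided 5% only if anxiety is significant. Week-5 results are secondary.
3. In Sample Size Planning, state that the 80% power applies to anxiety at that time point.

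**Cost.** A few lines of text and no added participants. Depression cannot be claimed if anxiety fails, so power to claim it falls from about 86% to about 69–78%.

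**Alternative.** Holm's procedure over the two outcomes at the primary time point avoids ranking them. Anxiety power at its first step (2.5%) is 71%. Over the whole procedure, if the outcomes are independent, it is 0.712 + (0.801 − 0.712) × 0.783 = 78% for anxiety and 0.783 + (0.858 − 0.783) × 0.712 = 84% for depression. Anxiety thus drops slightly below 80% while depression is better protected. If the sponsor wants both outcomes to be required, that rule should be stated and the sample size recomputed for joint power.
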